### Outcome Measures

Basic sociodemographic and medical data related to the pregnancy, birth and the mother's MS are collected from all participants (see Table 1). Combined with a questionnaire on stressful life events during pregnancy, this serves as a proxy for the mother's stress level during pregnancy. The child's current overall stress level is estimated using a questionnaire on stressful life events in the past 12 months (see Table 1). Time between GC exposure and assessment will be calculated using the child's age and the pregnancy week at the time of treatment. The primary outcome measure of this study is the child's global cognitive ability, as measured by a standardized IQ-test, i.e., the Reynolds Intellectual Assessment Scales and Screening (RIAS) (40). Secondary behavioral outcomes, such as motor development, attention, emotional excitability, ADHD-associated symptoms, and behavioral difficulties in multiple categories are measured via neuropsychological assessment, and self-, and informant-reported questionnaires. Additional secondary outcomes are obtained during the Trier Social Stress Test for children (TSST-C), an established standardized protocol to test stress sensitivity (41). These outcome measures comprise of the neuroendocrine (salivary cortisol) and autonomic stress response (salivary alpha-amylase concentration as a measure of sympathetic activity (42)) and heart rate variability (HRV) indices. To capture subjective stress levels during the TSST-C, the participant fills out an anxiety questionnaire (43) before and after the test. As measures of neurodevelopment, activation in the EEG during rest and a cognitive task included in the TSST-C and MRI-based markers of structural brain development are used. With the use of peripheral blood (leukocytes), and buccal mucosa cells, potential epigenetic mechanisms underlying changes in cognition and behavior as well as in stress sensitivity will be determined (see Table 2). For exploratory mechanistic analysis, the composition of the microbiome (stool sample), metabolome (EDTA plasma) and elementome (hair sample) will be examined.

**Table 1 T1:** Basic clinical and demographic data collected.

**Variables**	**Instruments/scale**
Demographic data of participant and guardian(s)	Demographic and socioeconomic data are collected from the participants and their guardian(s) with questionnaires and an interview, including age, sex, height, weight, guardians' education (highest degree), marital status, and chronic health conditions. Collected on NPT day.
Basic pregnancy and birth data	Pregnancy week at time of relapse and treatment is recorded for children exposed to GC. Birth data for the child (gestational age at birth, birth weight and length, head circumference at birth) and mother (diabetes mellitus and pre-eclampsia) are collected via an interview and the consultation of medical files. Collected on NPT day.
MS-specific medical data	To describe the mother's MS status during pregnancy, medical files and the mother are consulted regarding disease course and duration, therapies, and disease progression. Collected on NPT day.
Stressors during pregnancy (mother)	Based on similar validated instruments, a questionnaire adapted to this study's aims is used to assess stress during the pregnancy. For each trimester, the mother indicates any stressors related to personal, familial, or work life, or noxious substances intake. Collected on NPT day.
Recent stressors (child)	A German self-report questionnaire is used to determine stressful life events in the past 12 months of the child's life (Zürcher Life Events List) (44), involving home life, school, friendships, etc. In the affirmative case, the participant rates the level of stress the event caused on a 5-point scale. Collected on NPT day.

*NPT, Neuropsychological Testing*.

**Table 2 T2:** Primary and secondary outcome measures regarding the child.

**Variables**	**Instruments/scale**	**Expected outcome**
**Primary outcome measure**	
Intelligence quotient (IQ)	General cognitive ability is examined using the German version of the Reynolds Intellectual Assessment Scales and Screening (RIAS) (40). It examines facets of verbal and nonverbal intelligence and memory capacity. Collected on NPT day.	Lower IQ in GC-exposed children vs. control children
**Secondary outcome measures**	
Cognitive and behavioral performance	
Selective attention, vigilance, impulsivity	A continuous performance test (CPT) (45) is used to assess attentional performance in terms of selective attention, vigilance, and impulsivity. Collected on NPT day.	Worse performance in GC-exposed vs. control children
Motor development	To examine motor development, the Movement Assessment Battery for Children – Second Edition (M-ABC-2) (46) is used, which assesses the developmental adequacy of manual dexterity, ball skills, and balance. Collected on NPT day.	Worse motor development in GC-exposed vs. control children
Emotional excitability	To assess emotional excitability, the corresponding scale of a German self-report personality assessment for children (47) is used. Collected on NPT day.	Higher emotional excitability in GC-exposed vs. control children
Attention deficit disorder symptoms (attention, hyperactivity, and impulsivity)	A German parent-reported questionnaire is used to assess attention deficit hyperactivity disorder associated behavior (*FBB-ADHS* from *DISYPS-III*) (48). Collected on NPT day.	More or more-severe ADHD symptoms in GC-exposed vs. control children
Behavioral difficulties I	The German version of the parent-reported Child Behavior Checklist for children (*CBCL/6-18R*) (49) is used to examine behavioral symptoms on eight scales - (1) anxious/depressed, (2) withdrawn/depressed, (3) somatic complaints, (4) social problems, (5) thought, sleep, and repetitive behavior problems, (6) attention problems, (7) rule-breaking behavior, and (8) aggressive behavior. Collected on NPT day.	More or worse behavioral difficulties in GC-exposed vs. control children
Behavioral difficulties II	A parent-reported screening questionnaire, the German version of the Strengths and Difficulties Questionnaire (50) is used to assess emotional and behavioral problems, hyperactivity and inattention, peer relationship problems, and prosocial behavior. Collected on NPT day.	More or worse behavioral difficulties in GC-exposed vs. control children
Stress reactivity during the Trier Social Stress Test for children (TSST-C)		
Neuroendocrine stress response: salivary cortisol concentration	To determine HPAA activity at rest and during stress, a total of 9 saliva samples are collected throughout the TSST-C and at home (see Figure 2). Concentration of salivary cortisol will be estimated using a commercially available chemiluminescence immunoassay. Collected on NPT day and at home.	Higher HPAA activity in GC-exposed vs. control children
Autonomic stress response (ANS): salivary alpha-amylase concentration	The same 9 saliva samples are used to determine salivary alpha-amylase concentrations (marker for sympathetic activity) at rest and during stress. Concentrations will be estimated by an enzymatic colorimetric assay with an autoanalyzer. Collected on NPT day and at home.	Higher sympathetic activity in GC-exposed vs. control children
Autonomic stress response: heart rate variability (HRV)	Throughout the TSST-C, the participant's heart rate is recorded continuously using ECG (bipolar precordial Nehb lead). HRV indices will include linear and non-linear parameters. Collected on NPT day.	Shift toward a higher sympathetic tone in GC-exposed vs. control children
Subjective stress level	A German anxiety questionnaire (Kinder-Angst-Test-III) (43) is used to measure subjective levels of anxiety before and after the TSST-C (see Figure 2). Collected on NPT day.	Exploratory
Functional brain development	
Electrocortical activity	EEG recording is carried out continuously throughout the TSST-C, with electrodes placed on a standard cap according to the international 10–20 system. The activation patterns are evaluated using spectral power analysis (i.a. spectral edge frequency) and non-linear methods (12, 51). Collected on NPT day.	Higher spectral edge frequency in GC-exposed vs. control children
Structural brain development	
Structural *brain age*	The structural brain age is estimated with the help of the *BrainAGE Score* (52), which is based on a volumetric T1-MRI standard sequence. The *BrainAGE* score is a morphometric parameter that is derived from multivariate voxel-wise analyses based on a machine learning approach. Using this technique, the structural brain age is estimated with 1.5 years precision. Additional markers are gyrification and cortical thickness. Collected on MRI day.	Exploratory
Anatomical connectivity	Diffusion tensor imaging is used to examine complex structural networks that form the connectome, with a focus on regions particularly relevant to stress sensitivity, such as the limbic system including amygdala and hippocampus (29). Collected on MRI day.	Exploratory
Mechanisms underlying changes in cognition, behavior, and stress sensitivity		
Epigenetic mechanisms	Genome-wide and targeted candidate gene analysis of DNA methylation using advanced sequencing techniques (Illumina) on genes involved in the stress system and brain development (e.g., *NR3C1* and IGF2/H19 locus) (20). Material: peripheral blood (leukocytes) and buccal mucosa cells. Collected on NPT day.	Exploratory
Microbiome	Microbiota composition will be analyzed using high-throughput DNA sequencing techniques with fecal specimens collected with the Omnigene Gut OM-200 stool collector. Collected at home.	Exploratory
Metabolome	High throughput gene-sequencing (HTS) to explore potential links between antenatal GC exposure and the composition of the metabolome (17). Material: EDTA plasma. Collected on NPT day.	Exploratory
Elementome	Hair trace elementary profile analysis (*elementomics*) via inductively coupled plasma mass spectrometry to explore 47 mineral and toxic markers (53). Collected on NPT day.	Exploratory

*NPT, Neuropsychological Testing, GC, Glucocorticoid*.

### Procedure

Based on logistical considerations, eligible participants are invited to two study days (see Figure 1). On one of the days, neuropsychological testing (NPT) and the TSST-C take place (NPT day), while an MRI scan is carried out on the other (MRI day). For scheduling reasons, a few days may lie in between visits.

**Figure 1 F1:**
[figure not shown]
The two study days: testing sequence for all participants. MP, methylprednisolone; NPT, Neuropsychological testing; RIAS, Reynolds Intellectual Assessment Scales and Screening; CPT, Continuous Performance Test; M-ABC-2, Movement Assessment Battery for Children – Second Edition; PFK 9-14, German personality questionnaire; FBB-ADHS, German questionnaire for attention deficit hyperactivity disorder; CBCL/6-18, Child Behavior Checklist for children aged 6–18 years; SDQ-Deu-S, Strengths and Difficulties Questionnaire. MRI and NPT days may occur in reverse order.

On the NPT day, basic clinical and demographic data are recorded and the accompanying guardian is asked to assess their child's behavior using several well-established questionnaires (see Tables 1, 2). The participating child takes part in a set of four neuropsychological assessments of cognition and behavior (see Table 2), performed by a psychologist blinded to the participant's status of antenatal MP exposition. Before the participant is released for a 60-min break, hair, saliva, and buccal specimens are collected. The entire procedure takes ~120–180 min.

Following the collection of blood (see Table 2), stress sensitivity is examined using the TSST-C, an instrument to generate a psychophysiological stress response in the standardized setting of a simulated examination. See Figure 2 for a schematic representation of the procedure. The participant is equipped with EEG and ECG electrodes, a blood pressure monitor, and a pulse oximeter for continuous measurements during the TSST-C. Saliva samples are collected to measure cortisol and alpha-amylase concentrations throughout the test (see Figure 2 and Table 2 for scheduling of sampling). The TSST-C begins with an “active rest” phase of 15 min, during which the participant watches a slow-paced animal documentary, sitting down. In a separate room, a two-person examination committee then present the participant with a story, before leaving the room for 5 min, giving the participant time to prepare an “exciting and compelling” ending to the story. The participant is then asked to continue telling the story (stress phase I), after which the participant is instructed to verbalize serial subtractions of age-appropriate difficulty (stress phase II). When the participant makes a mistake, the examiner interrupts them with a prompt to start over. The stress phases last a combined 10 min, after which the participant receives positive feedback from the committee. In total, the TSST-C takes ~130 min. After the TSST-C, the participants are handed a kit for the at-home collection of a further 3 saliva samples, to capture the HPAA activity throughout a normal day. The kit also includes material to collect a stool sample for the analysis of the microbiome.

**Figure 2 F2:**
[figure not shown]
Schematic representation of TSST-C procedure. C1–C9, saliva swabs 1–9 (cortisol); α-A1–α-A9, saliva swabs 1–9 (alpha-amylase); RR1–RR8, blood pressure measurements 1–8; KAT-III, German anxiety scale for children (Kinder-Angst-Test-III) – versions P (prospective) and R (retrospective).

On the MRI day, a volumetric cranial MRI scan in T1 standard sequence is obtained from the participant. Diffusion tensor imaging (DTI) is used to determine the anatomical connectome. Including participant education, the entire procedure is estimated to take 50 min.

### Data Storage and Management

All data are recorded in a pseudonymised form. In accordance with EU data protection legislation, both study centers maintain a secured patient identification list with full names, addresses, and dates of birth. Any personal information is archived for at least 10 years after inclusion of the last participant.

The collection, management and use of human biological specimens in this study is in accordance with national and EU legislation. Any transfer of specimens between the two centers will take place in accordance with the Oviedo Convention (Convention on Human Rights and Biomedicine – CETS 164) and Recommendation of the Committee of Ministers to Member States on research on biological materials of human origin (adopted by the Committee of Ministers on 15 March 2006 at the 958th Meeting of Ministerial Deputies). Due to the vulnerable nature of a cohort of children, we further implement directive 95/46/EC and working group 8/2010 opinion, article 29 and take the high importance of data protection in vulnerable populations into careful consideration.

Part of the initial data collection uses hard copy files, which are stored in a secure location and later digitized using an electronic case report form. All digitized data are stored on a safe server managed by the Center for Clinical Studies at the University hospital in Jena.

### Data Analysis Plan

For the analysis of the primary outcome, exposed and non-exposed groups will be compared in terms of their performance on the IQ test using a linear regression model taking into account potential confounders, including antenatal exposure to MP, point in time of exposure, maternal age at birth, birth weight, and socioeconomic background. Exploratory analysis of secondary outcomes will be performed with a linear regression model. Those outcomes measured repeatedly throughout the course of the TSST-C will be evaluated as time series data with a linear mixed model, with time as a further independent factor. For this analysis, two models will be fitted to explore (1) overall mean activity throughout the TSST-C, as well as (2) the change from baseline, in which the stress response will be adjusted to the baseline value.

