## Methods and Analysis

### Study Design

This two-center, observational, cross-sectional study aims to recruit *N* = 80 children of mothers with MS. The exposed group (*n* = 40) will consist of children who were antenatally exposed to MP as part of maternal MS relapse therapy, while the control group (*n* = 40), will consist of children of mothers with MS, who were not exposed to MP. Assessment will take place at the University Hospital in Jena (UKJ) and the Ruhr University Bochum (RUB). The first participant was included on 19/10/2020 and the study is anticipated to continue until the end of 2024.

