### Sample Size

The aforementioned study by some of the authors (11) investigated cognitive performance, as measured by an IQ test, in two groups of 39 healthy children at the age of 8 years. Considering the lower biological activity of MP compared to BM, the cohort in the present study was exposed to a GC-dose up to 50-fold higher than in the study on the effects of BM. The higher dosage of MP will most likely expose a significant effect in two groups of the same size as the previous study.

As the present study uses a different IQ test, the planned sample size is further based on the standardized effect size Cohen's *d*, as a multiple of the standard deviation. The previous study found a mean difference in IQ score of 10.5 points (SD = 14.0). A two-sample *t*-test (α = 0.05) would have sufficient power of 82% (*d* = 0.71) to 87% (*d* = 0.75) with two groups of 35 children. This takes into account potential non-evaluability of five participants per group, e.g., in the case of artifacts or attrition. The planned regression models include seven variables, which, based on the *rule of ten* leads to a sufficient number of cases to produce robust results (39).

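### The primary IQ model adjusts for timing of exposure, which controls do not have; unless timing is centred or nested within the exposed, the exposure coefficient is not the group difference that was powered

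*Protocol article*

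**What the plan says.** Under Data Analysis Plan, the protocol article states that "exposed and non-exposed groups will be compared in terms of their performance on the IQ test using a linear regression model". The model is to take account of "potential confounders, including antenatal exposure to MP, point in time of exposure, maternal age at birth, birth weight, and socioeconomic background". The term being tested (exposure) and a property of that term (when it happened) therefore both appear in a list of confounders.

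Two other places show who has a value for timing. Study Design says that the control group "will consist of children of mothers with MS, who were not exposed to MP". Table 1, in the row on pregnancy and birth data, says "Pregnancy week at time of relapse and treatment is recorded for children exposed to GC". No coding for controls is given.

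The Sample Size section powers a different quantity, an unadjusted comparison of two means: "A two-sample *t*-test (α = 0.05) would have sufficient power". It claims "power of 82% (*d* = 0.71) to 87% (*d* = 0.75) with two groups of 35 children", with the larger effect size taken from a previous study (difference 10.5 points, SD 14.0).

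**The concern.** A confounder has to be defined in both groups and be related to group membership and outcome. Timing of exposure exists in one group only. It can modify the size of the effect among exposed children, but it cannot explain a difference between exposed and unexposed children. Calling it a confounder is therefore an error in the stated model, beyond any missing coding detail.

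Entered beside the exposure indicator without care, it changes what the exposure coefficient estimates and can inflate its standard error. This is the study's single primary analysis, and the Research Aims section wants the results to inform decisions about relapse treatment in pregnancy. If the coding is left open, materially different primary estimates could be obtained from the same data, and the choice among them could be made after the data are seen.

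**Working it through.** **Inputs from the article.** 35 evaluable children per group; alpha 0.05 (sidedness not stated; two-sided assumed because it reproduces the stated power); d = 0.71 and d = 10.5/14.0 = 0.75; controls unexposed; treatment week recorded for exposed children only.

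**Inputs assumed.** The article gives no distribution of treatment week. I used weeks spread evenly over 1–40, 4–38 or 4–28, a case with mean 16 and SD 8, and trimester splits of 15/15/5, 14/14/7 and 12/12/11 among 35 exposed children. The power figures take the effect as constant over timing.

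**Step 1: the plan's own figure.** In SD units, the standard error of the group difference is √(2/35) = 0.239. The noncentrality is 0.71/0.239 = 2.97 or 0.75/0.239 = 3.14. The noncentral t with 68 degrees of freedom gives 83.3% and 87.1%. The stated 82% and 87% are reproduced closely enough.

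**Step 2: controls coded 0.** Let E be exposure and T = E × week, with half the sample exposed and week having mean μ and SD σ among the exposed. Regressing E on T gives

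VIF = 1/(1 − R²) = 1 + μ²/(2σ²).

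The standard error of the exposure coefficient is multiplied by √VIF.

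| Timing among exposed (assumed) | μ, σ | VIF | Power, d = 0.71 | Power, d = 0.75 |
|---|---|---|---|---|
| Weeks 1–40 | 20.5, 11.6 | 2.6 | 45% | 49% |
| Mean 16, SD 8 | 16, 8 | 3.0 | 39% | 43% |
| Weeks 4–38 | 21.0, 10.1 | 3.2 | 38% | 41% |
| Weeks 4–28 | 16.0, 7.1 | 3.5 | 35% | 38% |
| Trimester scored 1–3, three splits | about 1.7–2.0, 0.7–0.8 | 3.9–4.0 | 31–32% | 34–35% |

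For the case with mean 16 and SD 8: VIF = 1 + 256/128 = 3.0, the standard error is 0.239 × √3 = 0.414, and the noncentralities are 1.71 and 1.81. A simulation of the 1–40 case at d = 0.75 (5,000 runs) gave 47%, against 49% by formula.

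The target also moves. If the true mean difference is −10.5 at mean week 16 and the effect changes by 0.3 points per week (an assumed slope), the coefficient at week 0 is −10.5 − 0.3 × 16 = −15.3, or −10.5 + 0.3 × 16 = −5.7 if the slope has the other sign.

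**Step 3: trimester indicators.** With exposure, an intercept and all three indicators, the columns are linearly dependent. With one indicator dropped, the exposure coefficient is the reference trimester against controls, with standard error √(1/35 + 1/r) for r children in that trimester. For r = 5 this is 0.478 and power is 31% to 34%. For r = 15 it is 0.309 and power is 62% to 67%. The other splits fall between.

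**Step 4: timing left missing for controls.** A complete-case fit drops every control. Exposure is then constant and its effect cannot be estimated.

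**Step 5: week centred at the exposed mean, controls set to 0.** T then has mean 0 in both groups, so it is uncorrelated with E and VIF = 1.0. Power is 83% and 87%, and the coefficient is the mean group difference. Leaving timing out gives the same; with seven variables and no collinearity, power is 83.2% and 87.0%.

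**The case against.** The strongest reply is that the loss belongs to a coding that the article never states. Centred or nested timing fits the published sentence as well as zero coding does, and it costs nothing. Dropping all controls would contradict the stated aim of comparing the groups. With trimester indicators, the frequency-weighted contrast of exposed with controls still has variance 1/35 + 1/35, so the group difference can be recovered in full if that contrast is the one tested. Even under zero coding, a joint 2-degree-of-freedom test of exposure and timing has power 74% (d = 0.71) to 79% (d = 0.75) when the effect is constant. A condensed article may also leave coding and contrasts to a fuller document that is not shown.

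All of this stands as a limit on the size of the problem. A reader might infer that the plan as written certainly loses about half its power, or that a true 10-point effect would usually be missed. The article does not support either: both follow from zero coding with a test of the single coefficient, under timing distributions that the article does not give.

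A reader might also extend the criticism to the interval from exposure to assessment and its near-identity with the child's age. Outcome Measures does say "Time between GC exposure and assessment will be calculated", but the Data Analysis Plan names neither that interval nor age among its covariates, so no such model is there to criticise.

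The reply does not reach the misclassification. A fuller document could supply a coding. It could not turn a variable that exists only among the exposed into a confounder of the comparison of exposed with unexposed.

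**Conclusion.** The concern holds in conditional form. The primary model names as a confounder a variable that is undefined for controls, and that statement needs correcting whatever coding is used. Unless timing is centred or nested within the exposed, the exposure coefficient is not the mean difference that the sample size section powers.

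The size depends on coding and on assumed timing distributions. Against 83% to 87% without timing, power for the exposure coefficient is about 31% to 49% with zero coding, about 31% to 67% with trimester indicators, and unchanged with centring. The shift of the estimate to about −15 or −6 rests on the assumed slope of 0.3 points per week and illustrates the mechanism only.

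**What to change.** Remove point in time of exposure from the primary model. State that exposure (yes/no) is the tested term and that the adjustment set holds only variables defined in both groups that could confound the comparison; exposure itself should not be listed as a confounder.

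Analyse timing as a secondary question within the exposed group. If it is to stay in the primary model, specify it as week centred at the exposed mean with controls set to 0, so that the exposure coefficient remains the mean group difference.

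The cost is a change of wording in the analysis plan, best made and dated before the data are analysed. No new data are needed, and the planned sample keeps its 83% to 87% power under the plan's own effect sizes.
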